**Figure 2: Development and standardization process of multipronged interventions**

**Intervention Standardization:** The steps of intervention standardization will include defining the type of standardization for each component and defining the limits of the standardization for each component^19^. The type and limits of the standardization will be set after consensus with the stakeholders and the project advisory group.

1. Type of standardization for each component and step can be classified into “mandatory” or “optional” or “prohibited”. “Mandatory” step must be performed under all circumstances and if not performed will be considered as protocol deviation; opposite is true for “Prohibited”. “Optional” step may or may not be performed at discretion of the participating surgeon.
2. Limits of standardization for each component can be set as “exactly” or “with boundaries” or “without boundaries (flexible)” based on the flexibility allowed for adoption by the health care professional. If mentioned as “with boundaries”, the component or step can be followed as per the amount of flexibility mentioned for each component of intervention. (Table -2)

**Intervention Monitoring:** The levels of fidelity will be defined and noted as per the levels mentioned in Table-1 after discussion with all the stakeholders. The discrepancy among the stakeholders will be resolved after discussion among each other for reaching to the final consensus. Based on the multipronged interventions, a checklist and standard data collection form will be developed. The check list developed will be used for assessing the level of fidelity and compliance to the multipronged interventions for each patient as shown is Appendix-I.

**Table-1**: Levels and type of intervention fidelity to be described for each component of the multipronged intervention^19^

| **Level of fidelity** | **Type and description** |
| --- | --- |
| Protocol deviation from intended intervention | Did not receive any intervention or received alternative intervention not being evaluated in the study |
| Deviation from component(s) of the intended intervention | Did not receive the component of the intervention or component of intervention delivered partially or component of intervention delivered in a different way than what is mentioned in the study protocol. |

The set of selected multipronged intervention package co-developed and standardized by all the stakeholders will be implemented among health care professionals.

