**C. Identification of SSIP/Stewardship Champions**: The “SSIP champions” will be identified for each setting by the site PI/Co-PI (could be ICN nurse/resident/surgeon who have leadership qualities and actively working in the surgery department). These SSIP champions will ensure the adoption of the multimodal interventions in their setting and will also assess the need of interim training or re-training in their respective sites. If the compliance to the multipronged interventions is not there at a particular site as assessed by the checklist of each patient, then re-training will be schedule. If non-compliance is persistent, then it will be communicated to the project advisory group. The process evaluation will be done by project advisory group and IDI will be conducted to understand the hurdles and challenges in adoption of these interventions and explained below.

**Process evaluation**: The compliance to the multipronged interventions as assessed by the SSIP champions will be evaluated by the project advisory committee. The SSIP champions will also evaluate whether the structural and system changes are in-place at respective sites and behavioural changes are adopted by the health care professionals. If there is non-compliance and is persistent, then the stakeholders will re-assess the acceptance of the co-developed multipronged interventions. In-depth interviews with the health care professionals will follow to understand the hurdles and challenges in accepting these interventions and troubleshooting iteratively. The multipronged interventions will be either adapted as per the challenges evolving or co-developed as per the site need or if only retraining will suffice, then re-training will be planned. The monitoring of the compliance to the multipronged interventions at each site using the checklist will be done by SSIP champions and reported to the project advisory group quarterly.

The intervention will continue with the help of SSI Champions and after the study is over also. The intervention and result assessment quarterly will go hand in hand and the impact assessment will follow.

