**Post-intervention Phase**:

This phase will involve the data collection on the same parameters as in pre-intervention phase using the CRF and check the implementation of multipronged intervention packages using the checklist developed based on the multipronged interventions. The SSIP champions will evaluate whether these multipronged interventions are adopted adequately in their respective setting. Intermittent weekly reminders like e-posters, WhatsApp messages will be given to health care professionals for adoption of the multimodal interventions which will act as re-enforcement reminders. Interim training sessions will be planned after every 6 months (in case new staff is recruited or compliance to interventions reduces).

In-depth interviews will be conducted with key stakeholders (surgeons, health care professionals and nursing officials involved) to evaluate their perception of impact and feasibility of interventions at 6 months post-intervention phase and suggestions to improve the multipronged interventions.

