### Early Termination Study Visit

The site(s) which is/are not complying with the study procedure and the surgeons not following the multimodal interventions as required, will be terminated from the study. No further data collection will be done for that site.

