# STUDY ADMINISTRATION

## Data collection and management

Patients planned for general surgical procedures (elective or emergency) will be screened for inclusion in the study based on inclusion and exclusion criteria.

The data collection during baseline, post-intervention phase for the surgical patients undergoing elective or emergency surgery will be done by the Infection control nurse and research fellow in the standardized data collection form including but not limited to the data on timing of antimicrobial prophylaxis given, time of start of surgery, vitals, re-dosing of antimicrobial prophylaxis, time of stoppage of surgery, type of surgery (name of surgery; clean/clean-contaminated/contaminated/dirty), aseptic precautions taken or not, information on drains in situ, post-operative care, details of post-operative antimicrobials. The patient will be followed up regularly till discharge and data on SSI, antimicrobials, clinical outcome will be recorded. The patient will be called in-person for follow-up to ODP at 30-day to know the clinical status and outcome of the patient. Any unplanned visit to OPD or emergency will be noted with the reason of the visit.

If follow-up is not possible at 30 days after surgery, patients will be followed up as soon after this as possible or telephonically. If patient developed SSI before postoperative day 30, they will still be reviewed at 30 days after surgery to record secondary outcomes.

In intervention phase, in addition the checklist of multipronged interventions will be checked for implementation assurance along with the data collection form.

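### Champions charged with securing adoption also assess compliance, and no independent checklist scorer is named, so fidelity may be overstated

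*Protocol*

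**What the plan says.** In the protocol, section 3.1.3 (part C) gives the champions a delivery role: "These SSIP champions will ensure the adoption of the multimodal interventions in their setting". They are chosen by the site PI or Co-PI, and a champion "could be ICN nurse/resident/surgeon who have leadership qualities and actively working in the surgery department". The process evaluation paragraph of the same section gives them the measuring role as well: "The monitoring of the compliance to the multipronged interventions at each site using the checklist will be done by SSIP champions", with quarterly reports to the project advisory group. Section 3.1.4 continues this after deployment: "The SSIP champions will evaluate whether these multipronged interventions are adopted adequately in their respective setting".

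Section 3.1.2 (Intervention Monitoring) explains what the checklist is for: "The check list developed will be used for assessing the level of fidelity and compliance to the multipronged interventions for each patient".

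Section 4.1 says that patient data collection "will be done by the Infection control nurse and research fellow in the standardized data collection form". It then adds: "In intervention phase, in addition the checklist of multipronged interventions will be checked for implementation assurance along with the data collection form". That sentence does not say who does the checking.

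Section 3.9 plans a subgroup analysis by level of fidelity. Section 3.5.1 provides that non-complying sites and "the surgeons not following the multimodal interventions as required, will be terminated from the study".

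**The concern.** A person asked to make a programme succeed should not be the one who records whether it was followed, least of all for their own operations. Marginal or missed steps tend to be given the benefit of the doubt, and the resulting error runs in one direction. The protocol allows this arrangement and describes no independent or duplicate scoring.

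The unnamed scorer in section 4.1 adds a second problem. One site could have study staff complete the checklist while another leaves it to a surgeon-champion, and both would be following the protocol. Differences in fidelity between sites would then partly reflect who held the pen.

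Three uses of the score are at stake: the re-training, escalation and adaptation decisions in section 3.1.3, which would come late if misses go unrecorded; the process evaluation; and the fidelity subgroup analysis, where patients wrongly placed in the compliant group dilute the contrast.

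**Working it through.** The protocol gives no compliance rate or scoring error rate, so there is no plan figure to reproduce. The check is a reading of the passages, followed by an illustration on assumed inputs.

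**Step 1: who does what.**

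| Task | Section | Person named |
|---|---|---|
| Secure adoption | 3.1.3, part C | Champion |
| Monitor compliance by checklist | 3.1.3, process evaluation | Champion |
| Judge adequacy of adoption | 3.1.4 | Champion |
| Complete the data form | 4.1 | Infection control nurse and research fellow |
| Check the checklist | 4.1 | Nobody named |
| Review the champions' assessments | 3.1.3 | Project advisory committee |

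Delivery and assessment meet in the champion. Section 4.1 does not separate them, because it names no one for the checklist and because an infection control nurse may also be the champion.

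**Step 2: what depends on the score.** The per-patient fidelity level (3.1.2), re-training and escalation (3.1.3) and the fidelity subgroup (3.9) depend on it. The primary endpoint (3.7) and its pre-post comparison (3.9) do not.

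**Step 3: possible size, on assumed inputs.** Let c be true compliance and f the share of missed items scored as done, with no completed item scored as missed. Then

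- recorded compliance = c + (1 − c) × f
- share of the recorded-compliant group that is wrong = 1 − c / recorded compliance

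| True c | f = 0 | f = 10% | f = 30% |
|---|---|---|---|
| 50% | 50% | 55% (9.1% wrong) | 65% (23.1% wrong) |
| 70% | 70% | 73% (4.1% wrong) | 79% (11.4% wrong) |
| 90% | 90% | 91% (1.1% wrong) | 93% (3.2% wrong) |

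For example, 0.50 + 0.50 × 0.30 = 0.65, and 1 − 0.50/0.65 = 23.1%. The overstatement runs from 0 to 15 points over this grid.

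The site effect can be read from the middle row. Two sites both truly at 70%, one scored without error and one with f = 30%, would report 70% and 79%. The scorer alone creates a gap of 9 points.

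**Step 4: effect on the subgroup contrast, on a more severe assumption.** Take c = 60% and f = 50%, with SSI rates of 6% in truly compliant and 10% in non-compliant patients (all assumed).

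- Recorded compliance: 0.60 + 0.40 × 0.50 = 80%
- Wrongly in the compliant group: 0.20 / 0.80 = 25%
- SSI rate in that group: (0.60 × 6% + 0.20 × 10%) / 0.80 = 7.0%

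The contrast falls from 4 points (6% v 10%) to 3 points (7% v 10%), a quarter smaller. This assumes that wrongly scored patients carry the non-compliant SSI rate.

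**The case against.** The strongest reply is that the plan already contains checks.

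- The Appendix-I template checklist records dose time, start and end of surgery, agent and last dose beside the yes/no answer. All three steps marked mandatory in the template are antimicrobial items with such entries.
- The data form in section 4.1 separately captures prophylaxis timing, surgery times and post-operative antimicrobials.
- The advisory committee evaluates the champions' assessments, and the advisory group includes an external implementation expert.
- Single-dose use, prolonged prophylaxis, irrational combinations and days of therapy are secondary endpoints in both periods (3.8) and do not rely on the champion's score.

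This stands in part: many antimicrobial items could be verified. The checks are incomplete, however. The template item covering skin preparation, aseptic precautions and hand hygiene records only the skin agent. The final package need not match the template. The advisory group includes the site PIs and reviews what champions report; no re-scoring is described.

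A reader might also infer that sections 3.1.3 and 4.1 contradict each other. They do not. Section 4.1 assigns the data form, not the checklist, to the nurse and fellow, and monitoring in 3.1.3 could mean reviewing checklists that others completed. The assignment is unclear. Nor does section 3.5.1 say that the champion's checklist triggers termination, so that incentive is plausible but not written down as such.

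Finally, the monitoring plan is still to be settled after co-development, and the scorer could be named then. That is a reason why the change is easy, but section 3.1.3 already gives the assessment to the champions.

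**Conclusion.** The point holds as a risk. The protocol lets those responsible for adoption assess it, possibly on their own cases, and does not fix who scores the checklist. Fidelity may be overstated, by an amount the documents do not allow anyone to estimate; the figures above rest wholly on assumed compliance, scoring error and SSI rates, and with no scoring error there is no overstatement.

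Two stronger conclusions are tempting and not supported. One is that fidelity will be overstated: the recorded times and agents and the advisory review may hold the error down. The other is that a null SSI result could not be interpreted: the prophylaxis endpoints show uptake of important components without the checklist score. They do not cover the non-antimicrobial components, so interpretation would be weakened there but not lost. The consequences are confined to the process evaluation, the triggers and the fidelity subgroup. This is an inexpensive improvement worth making before deployment, and it does not threaten the primary comparison.

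**What to change.** State the same rule in sections 3.1.2, 3.1.3 and 4.1:

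- Each patient's checklist is scored by a project-funded staff member (project nurse or project technical support) who is neither the champion nor on the operating team.
- The scorer works from the recorded times and agents where these exist.
- The champion receives the results for feedback and re-training but scores no patient. The champions' site-level evaluation in section 3.1.4 then rests on those scores.

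The cost is protocol wording and a small added task. The budget in section 6 funds both posts at all seven centres (4 + 3 by allowance band). Section 4.1 uses other titles (infection control nurse, research fellow), so the wording should say which funded post is meant. The one restriction on sites is that the checklist scorer may not be appointed champion.

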### Phase-IV (Impact assessment and results dissemination):

Phase-IV involve the post-intervention phase for assessing the impact of adoption of the multipronged interventions in prevention of SSIs and the dissemination phase.

**Post-intervention Phase**:

This phase will involve the data collection on the same parameters as in pre-intervention phase using the CRF and check the implementation of multipronged intervention packages using the checklist developed based on the multipronged interventions. The SSIP champions will evaluate whether these multipronged interventions are adopted adequately in their respective setting. Intermittent weekly reminders like e-posters, WhatsApp messages will be given to health care professionals for adoption of the multimodal interventions which will act as re-enforcement reminders. Interim training sessions will be planned after every 6 months (in case new staff is recruited or compliance to interventions reduces).

In-depth interviews will be conducted with key stakeholders (surgeons, health care professionals and nursing officials involved) to evaluate their perception of impact and feasibility of interventions at 6 months post-intervention phase and suggestions to improve the multipronged interventions.

**Dissemination Phase:**

The report of the project will be presented to the Head of the Institute of the respective institute and project advisory group. The results will be published in the indexed journal as mentioned in Section 5 “Publication Plans” below.

**Figure-3**: Study plan and duration of each phase of the study

### Supervision of the study implementation:

The project advisory group (PAG) will maintain the audit trail of all the activities done in their respective sites. Periodic meetings will be planned (physical or virtual with all the stakeholders and they will be appraised of the project activities. The plan is to have at least 5 physical meetings with all stakeholders (one before starting the study, three during study and one after study completion). The implementation plan will be continuously evolved with the inputs for the project advisory group and external experts in implementation research.

## Allocation to Treatment Groups and Blinding (if applicable)

Not applicable

## Study Duration, Enrollment and Number of Sites

### Duration of Study Participation

The study participation will last for 30-days or 90 days if implant placement during surgery. Each subject will be included in the study on pre-operative day-1 and followed till discharge. After discharge, the patient will be reviewed in the OPD or followed up telephonically till 30-days of the surgery or 90 days if implant placed (where the day of surgery will be taken as POD-0) for any evidence of surgical site infection. Any re-admission in-between the discharge and 30-days will be noted along with the reason of re-admission.

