## Subject Completion/Withdrawal

The patients who take leave from hospital against medical advice (LAMA) will be contacted for follow-up at 30-days for the outcome.

If follow-up is not possible at 30 days after surgery, patients will be followed up as soon after this as possible.

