# Appendix-I: Template example of the components of Multipronged interventions and CheckLIST to be checked for each patient

The intervention components can be chosen based on observed practices in the clinical setting, gap analysis, the global guidelines for prevention of surgical site infections by WHO^2^, second edition 2018 and Clinical practice guidelines for antimicrobial prophylaxis in surgery which were recommended with “Strong” recommendations and “Moderate to Good” quality of evidence and easy to implement in the setting.

**Table-2:** Template intervention package (not necessarily the same interventions mentioned below)

| **Components of multipronged Intervention** | **Steps of the Intervention** | **Type of standardization** | **Limits of standardization** |
| --- | --- | --- | --- |
| Interventions for surgical infection prevention: four system interventions | Delivery of intravenous antimicrobial prophylaxis within 1 hour before incision (2 hour for vancomycin and fluoroquinolones) | Mandatory | Boundaries (Flexibility in choosing antimicrobial by the surgeon based on the type of surgery, patient factors, clinical practice and guidance documents) |
|  | Redosing of antimicrobial if interval >2 half-lives or if blood loss >1500 ml | Optional | Boundaries (Flexibility based on the duration of the surgery and type of the antimicrobial agent chosen for surgical prophylaxis) |
|  | Use of antimicrobial prophylactic agent consistent with published guidelines (Global guidelines for prevention of surgical site infections by WHO^2^, second edition 2018 and Clinical practice guidelines for antimicrobial prophylaxis in surgery^10^) | Mandatory | Boundaries (Flexibility in choosing antimicrobial by the surgeon based on the type of surgery, patient factors, clinical practice and guidance documents) |
|  | Discontinuation of prophylactic antimicrobial agent within 24 hours of surgery (within 48 hours for cardiothoracic procedures in adult patients): Post operative day- 1(POD-1) review | Mandatory | Flexibility allowed till 24 hours postoperative |
| Interventions for surgical care improvement: five behavioral interventions | Proper hair removal: No removal (if not hampering surgery) or use of clippers/depilator method. | Optional | Boundaries (Flexibility in choosing no removal or clippers or depilators) |
|  | Use of razors for hair removal | Prohibited (Considered inappropriate if razors used for hair removal) | Exactly (Not flexible) |

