| 8 | Maintenance of perioperative normothermia (≥35.5°C) in surgical patients who have anesthesia >60 minutes | Temperature in intra-operative period ………….. |  |
| 9 | POD-1 review of antimicrobials. | Any advice given: ……………………………….  Advice followed or not? …………………………….. |  |
| 10 | SSI surveillance as per CDC/NHSN definition of SSI. | SSI surveillance done as per definition mentioned in Appendix-II …………….. |  |

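### Two sections set different rules for finding SSIs after discharge, and SSI surveillance is on a checklist used in one phase only, so a difference in detection between phases is left possible

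*Protocol*

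**What the plan says.** Three sections of the Protocol describe contact after discharge.

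- Section 3.3.1 (Duration of Study Participation): "After discharge, the patient will be reviewed in the OPD or followed up telephonically till 30-days of the surgery", extended to 90 days where an implant is placed. The two modes are offered without an order of preference.
- Section 4.1 (Data collection and management): "The patient will be called in-person for follow-up to ODP at 30-day to know the clinical status and outcome of the patient". The fallback follows: "If follow-up is not possible at 30 days after surgery, patients will be followed up as soon after this as possible or telephonically". No visit at day 90 is named.
- Section 3.5 (Subject Completion/Withdrawal): "If follow-up is not possible at 30 days after surgery, patients will be followed up as soon after this as possible". The telephone is not mentioned.

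On the checklist, section 4.1 states: "In intervention phase, in addition the checklist of multipronged interventions will be checked for implementation assurance along with the data collection form". Item 10 of the template checklist (Appendix-I, Table-3) reads "SSI surveillance as per CDC/NHSN definition of SSI". Under section 3.1.3, poor compliance on the checklist leads to re-training and, if it persists, referral to the project advisory group, with quarterly reporting.

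Other statements point towards uniformity. For the post-intervention phase, section 3.1.4 says: "This phase will involve the data collection on the same parameters as in pre-intervention phase using the CRF". Section 3.7 applies the CDC definition to both phases. Section 4.1 has the infection control nurse and research fellow collect data in both. The package table in Appendix-I is headed "Template intervention package (not necessarily the same interventions mentioned below)", so its content is not final.

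**The concern.** The primary endpoint is SSI to day 30 (day 90 with an implant), compared before and after the intervention. There is no concurrent control, and section 3.2 gives allocation and blinding as not applicable. Many of these infections may appear after discharge, so the post-discharge contact is part of the measuring instrument.

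Mode of contact can matter. Several routes in Appendix-III involve examining or sampling the wound, or a clinician's decision. A caller can learn of symptoms, or of a diagnosis made elsewhere, but cannot inspect or culture a wound. The Protocol gives no telephone script and no rule for bringing in a patient who reports symptoms.

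A site that telephones everyone satisfies section 3.3.1 but not section 4.1. If practice drifted between phases, or if ticking a surveillance item made case-finding more complete in the intervention phase, the observed rates would change with no change in true risk. More telephone contact afterwards would exaggerate a benefit; more complete surveillance afterwards would hide one. A later analysis plan could not repair this if contact mode had not been recorded at baseline.

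**Working it through.** **1. The rules side by side**

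| | Section 3.3.1 | Section 3.5 | Section 4.1 |
|---|---|---|---|
| Default | Clinic or telephone, equal | Not stated | Clinic visit at day 30 |
| If day 30 is missed | Not stated | Later contact | Later contact or telephone |
| Day 90, implant | Clinic or telephone | Not stated | Not stated |

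Sections 3.3.1 and 4.1 conflict on whether the telephone is an equal option or a fallback. For implant patients at day 90, only the either/or wording applies.

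**2. The planned sample sizes (section 3.11)**

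Inputs from the Protocol: 8% vs 5% (clean), 12% vs 8% (clean-contaminated), 30% vs 20% (contaminated); two-sided 5%; 90% power; 15% loss.

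Formula, with p̄ the mean of the two rates:

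n = [1.96·√(2p̄(1−p̄)) + 1.2816·√(p1(1−p1) + p2(1−p2))]² / (p1−p2)²

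This gives 1418, 1181 and 392 per phase before loss. Multiplying by 1.15 gives 1631, 1359 and 451; dividing by 0.85 gives 1669, 1390 and 462. Both are within 3% of the stated 1630, 1350 and 450, so the same formula can be used for what follows. With 85% evaluable (1385, 1147 and 382 per phase), power is 89.3%, 89.2% and 89.3%.

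**3. Effect of unequal detection**

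The Protocol gives no detection share for either mode, so these shares are assumptions, shown as a range. Observed rate = true rate × share detected in that phase. The probability of a significant result in the stated direction is

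Φ{[d − 1.96·√(2p̄(1−p̄)/n)] / √[(p1(1−p1) + p2(1−p2))/n]}

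where p1 and p2 are the observed rates and d is their difference. Example: clean, no true effect, 100% detected before and 90% after. The observed rates are 8.0% and 7.2%, d = 0.008, n = 1385, and both standard errors are about 0.0101. Φ[(0.008 − 1.96 × 0.0101)/0.0101] = Φ(−1.17) = 12.2%.

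| Scenario | Clean | Clean-contaminated | Contaminated |
|---|---|---|---|
| No effect, 100% before, 95% after: false reduction | 5.8% | 6.5% | 6.6% |
| No effect, 100% before, 90% after | 12.2% | 14.6% | 14.9% |
| No effect, 100% before, 80% after | 37.0% | 45.7% | 46.3% |
| Planned effect, 90% before, 100% after: power | 68% | 63% | 63% |
| Planned effect, 80% before, 100% after: power | 36% | 27% | 27% |

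The nominal chance of a false reduction is 2.5%.

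**4. What change in contact mode a 10% loss would need**

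Assume that a call finds 70% of what a visit finds. Starting from visits only, the loss in detection is 0.30 × telephone share × share of SSIs arising after discharge. A loss of 0.10 needs a telephone share of 0.10/0.30 = 33% if all SSIs arise after discharge, and 0.10/(0.30 × 0.5) = 67% if half do. The 90% row therefore stands for a substantial shift in practice.

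**The case against.** The strongest reply is that nothing in the text makes the phases differ. The follow-up wording, conflicting or not, applies to both alike. The CRF parameters, data collectors and CDC definition are common to both, and section 6 budgets a dedicated project nurse at each centre over the three project years, partly for the 30/90-day follow-up. Sections 3.3.1 and 4.1 can also be read together, with both modes available and the visit preferred at day 30. This largely stands: the difference is a possibility left open, not something the plan sets. It does not remove the problem, because common parameters fix what is recorded, not how the patient is reached.

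Three stronger readings are tempting and are not supported.

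- A reader might infer that section 4.1 requires a visit. It does not; it allows later or telephone contact when day-30 follow-up is not possible.
- A reader might infer that outcome detection is part of the intervention. SSI surveillance is not among the package components in Table-2. It appears only on the Table-3 template checklist, which may change, and SSI is also collected at baseline. What is confined to one phase is the check, not the surveillance.
- A reader might infer that the CDC criteria cannot be met by telephone. They are alternatives, and a patient can report drainage, or a wound opened or diagnosed by a doctor. Readmissions and unplanned visits are also recorded.

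It is also fair that the CRF is not shown and its listed items are open-ended, so a contact-mode field may exist. The listed items do not include one.

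**Conclusion.** The point holds as a specific, cheaply repaired weakness in how the primary endpoint is ascertained. Sections 3.3.1 and 4.1 give different rules, section 4.1 leaves day 90 unaddressed for implant patients, and completeness of surveillance is checked in the intervention phase only, as the template stands. Because the comparison is uncontrolled, any resulting difference in detection would pass straight into the 3, 4 or 10 point contrast, with unknown sign.

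The size is illustrative only. Under the assumed fall in detection from 100% to 90%, the chance of a false significant reduction is 12-15%; under the reverse change, power falls from about 89% to 63-68%. These figures rest on assumed detection shares, the planned event rates and 85% evaluable patients. They show sensitivity and do not predict what will happen. The change should be made before baseline collection, since contact mode not recorded then may not be recoverable.

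**What to change.** 1. Reconcile sections 3.3.1, 3.5 and 4.1 into one ascertainment rule, applied identically in both phases and covering day 30 and, for implants, day 90: clinic review first, telephone as fallback. Calls should use a fixed symptom script drawn from Appendix-III, with clinic review of any positive answer.
2. Record contact mode and SSI onset date on the CRF from the start of baseline, so that an SSI found at a late contact is counted only if its onset lies within the window. Report contact mode by phase.
3. Take item 10 off the intervention-only checklist, or apply the same surveillance check in both phases.

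An analysis limited to patients seen in person is at most supplementary, because attendance may itself depend on wound problems.

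The cost is protocol wording, one script, the CRF entries and some extra clinic recalls after positive calls. The sample size does not change.
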